### Data collection

We will collect participant data from intervention and comparison arms at baseline just prior to randomisation and at three- and six-months post intervention (see Fig. 2 for the study schedule). Informed verbal consent will be obtained from trial participants during our telephone screening by our study coordinates and informed written consent will be obtained by outcome assessors just prior to the pre-treatment assessment. Patients will be sent the consent form 24 h before giving verbal consent and therefore more than 24 h before giving written consent. We will use validated performance tasks and questionnaires and inform all participants that if they decide to withdraw from the study, the data already provided will be retained and used in the analyses unless they request otherwise and that a post-interventional assessment is planned even if they didn’t finish the study.

**Fig. 2 Fig2:**
[figure not shown]
Study schedule. 1) Fatigue severity (FSS), age 2) PCSF*, FSS*, DSQ-PEM*, HADS, EQ-5D 5L, SSD-12, JSS*,* exercise vital sign*, SSS8, SSD12, SF12, MPI-D, Pain drawings, subjective theory for illness (items marked with * will also be assessed at follow up) 3) hand grip strength, 6 min walk test, *TMT, Stroop-test, N-back-test, Digit span-test* 4) TGIC (nur T1), PGIC, adverse events

For the collection of patient-reported outcome measures as well as demographic and health data, we will use an electronic survey conducted in REDCAP. All data will automatically be updated to this database. For the collection of data from our assessments, we will use standardised paper-based checklists and sheets for all paper-based tasks. Data obtained from assessments will be manually uploaded to REDCAP. To ensure date quality, the data monitoring board will randomly choose patient files to assess whether data in REDCAP is identical to data in assessment-checklists and in sheets used for paper-based tasks.

### Data management

Responsibility for data management will be held by an independent data manager, which will not be involved in either the assessments or the delivery of therapies. Data are collected, managed, and stored in the central database under the supervision and responsibility of the data manager. The data manager ensures that all legal requirements for data protection are met and that data quality, sharing, and security (e.g., integrity of randomization) are maintained during all phases of the study. Data collected from patients after giving verbal but before giving written consent will be deleted if patients do not proceed to give written consent. In accordance with GCP guidelines, we ensure that all data and study documents are pseudonymized and retained for at least 15 years after study completion. All participants will receive a code number as a pseudonym and all records that contain names or other personal identifiers will be stored separately.

### Measures

At baseline, we will assess demographic and clinical characteristics, including age, gender, marital status, education level, employment status, physical health status, chronic medical disease, history of fatigue/depression/anxiety, current and past psychiatric treatment/psychotherapy, current and past psychopharmacological treatment, willingness to accept active training and willingness to accept psychosocial treatment. In addition, a specific `COVID-19 module´ is included that records information on the severity and course of acute COVID-19 infection, the development of Post-COVID symptoms after infection, and vaccination status.

Impairment of physical and mental abilities due to COVID-19 infection is classified using the Post-COVID-19 Functional Status Scale (PCFS) [25–27]. The PCFS focuses on assessing the limitations in daily living associated with persistent symptoms after COVID-19 infection. The scale covers the full spectrum of functional limitations from grade 0, "no functional limitations," to grade 4, "severe functional limitations," and grade 5, "death." Studies have demonstrated good construct validity of the PCFS scale in highly symptomatic adult subjects with confirmed and suspected COVID-19 infection three months after symptom onset [26].

Patient Reported Outcomes (PROMs):*Fatigue*: Fatigue symptom severity will be assessed at each timepoint using the German version of the Fatigue Severity Scale (FSS) [39]. The FSS is an established Patient Reported Outcome (PRO) instrument for assessing the severity of fatigue and its impact on a person's activities and lifestyle in patients with a variety of medical conditions [38]. The subject is asked to rate the severity of the fatigue symptoms experienced in the last week using a numeric scale ranging from 1 (strong disagreement with the statement) to 7 (strong agreement with the statement). It includes nine statements that describe the severity and impact of fatigue. FSS total scores are usually reported as the mean of the nine items (range 9—63); a higher score indicates higher fatigue severity. According to published cut-off scores for the FSS, a further distinction can be made between mild/no fatigue (FSS total score ≤ 35), moderate fatigue (36 ≤ FSS total score ≤ 52), and severe fatigue (FSS total score ≥ 53) [23, 24]. Acceptable reliability, internal consistency, sensitivity, and good responsiveness to change have been demonstrated for people with chronic fatigue in physical illness [38].*Post-exertional Malaise*: Presence and severity of PEM will be measured using the German version of the DePaul Symptom Questionnaire—Post-exertional Malaise (DSQ-PEM) [41, 60]. The first five items assess the frequency and severity of PEM over a six-month period. Frequency is rated on a 5-point Likert scale (0 = not at all, 1 = a little, 2 = about half the time, 3 = most of the time, and 4 = all of the time. Participants rated the severity of each symptom on a 5-point Likert scale: 0 = symptom absent, 1 = mild, 2 = moderate, 3 = severe, 4 = very severe). The DSQ-PEM has been shown to have good test–retest reliability, and these five DSQ PEM items have good internal reliability (α = 0.84) [61]. Three additional PEM items assess the duration of symptom worsening after physical and mental activity. Good test–retest reliability was found for these items on symptom exacerbation by physical activity (k = 0.84) and symptom exacerbation by mental activity (k = 0.74) [61]. The fourth additional PEM item assessed how quickly patients recover from activities typically undertaken by healthy individuals. This item has previously been shown to have good test–retest reliability (k = 0.88) [61]. The fifth additional PEM item assessed whether participants did not exercise because it worsened their symptoms. Good test–retest reliability was also demonstrated for this item (k = 0.79) [61]. A score above a threshold for one or more of the first five DSQ-PEM items is considered in level-1 assessment. A threshold score of 2 to 4 for frequency (half of the time, most of the time, or all of the time) combined with a score of 2 to 4 for severity (moderate, severe, or very severe) for the same item is indicative of PEM. This method is recommended by the Common Data Elements PEM Working Group of the National Institute of Neurological Disorders and Stroke (part of the National Institutes of Health) [62]. Level-2 assessment was developed to further operationalize the Common Data Elements recommendations [41] and includes additional questions related to rapid recovery, exacerbation of stress, and PEM duration. Item 7 or 8 must be answered "yes," and item 9 requires a response of ≥ 14 h [4].*Emotional Distress*: The level of anxiety and depression of the last week will be assessed via the Hospital Anxiety and Depression Scale (HADS). With 14 items, the HADS is a self-assessment scale that measures anxiety and depression through two subscales. Seven items for each subscale are rated by the patient on a 4-stage response format. It was particularly developed for somatic disorders and physical symptoms were therefore excluded. The HADS has high validity and reliability [40].*Health-related quality of life*: We will assess health-related quality of life using the SF-12 and EQ-5D 5L questionnaires [50, 51]. The SF-12 is a widely used general health questionnaire that consists of a mental component and a physical component and has demonstrated its psychometric robustness in numerous studies. Overall sum scores are in the range of 0 to 100 with higher scores indicating better quality of life. The EQ-5D 5L is a standardised instrument for measuring generic health status and comprises five dimensions: mobility, self-care, usual activities, pain/discomfort, and anxiety/depression [51]. The patient rates each dimension on 5 levels: no problems, slight problems, moderate problems, severe problems, and extreme problems. To calculate quality-adjusted life years, the EQ-5D preference weights which are EQ-5D health states evaluated with a German tariff are combined with time [63].*Global impression of change*: Global impression of change will be assessed from both the patient’s (patient’s global impression of change, PGIC) and the therapist’s´ perspective (therapist’s global impression of change, TGIC). It is a 7-point scale with answers coded from “very much improved” to “very much worse”.*Burden of somatic complaints:* We will measure burden of specific somatic complaints using the SSD-12 [47, 48] and the SSS8 [49].

The SSD-12 comprises 12 items that require respondents to rate how frequently they experience each cognition, emotion, or behaviour on a 5-point Likert scale (from 0 = “never” to 4 = “very often”). Overall sum scores are in the range of 0 to 48 and provide a three-dimensional measure of the psychological criteria of DSM-5 Somatic Symptom Disorder. The SSD-12 displays high internal consistency (Cronbach’s α = 0.94) and good convergent validity, correlating well with measures of somatoform complaints, depression, and anxiety.

*The SSS8 *[49] is a validated measure of somatic symptom burden. It contains 8 items, asking participants "During the past 7 days, how much have you been bothered by any of the following problems?" concerning gastrointestinal, pain, fatigue, and cardiopulmonary aspects. Items are scored on a 5-point Likert scale (0=Not at all, 1=A little bit, 2=Somewhat, 3=Quite a bit, 4=Very much). Somatic symptom scoring ranges from 0-32 [(no to minimal (0-3 points), low (4-7 points), medium (8-11 points), high (12-15 points), and very high (16-32 points)]. It has good sensitivity to change with a minimal clinically important difference (MCID) of 3-points [64].

The SSD-12 and the SSS8 in combination provide good diagnostic accuracy (SSS-8 + SSD-12: AUC = 0.79; 95% CI = 0.74-0.84) [65] for somatoform disorders.*The Exercise vital sign *[43] is a brief measure to estimate physical activity. It contains two items asking 1) “On average, how many days per week do you engage in moderate-to-vigorous physical activity (like a brisk walk)?” and 2) “On average, how many minutes do you engage in physical activity at this level?”. Since the most frequently used measure for physical activity, the International Physical Activity Questionnaire (IPAQ), is under criticism for not being a valid measure of physical activity [66] we found the exercise vital sign as a brief self-reported measure in combination with giving the patients pedometers to count steps in their daily lives the best fit for our study.*Sleep problems*: The Jenkins Sleep scale (JSS) [42] is a simple and non-time-consuming measure for the most common symptoms of sleep disorders. The instrument includes four items measuring quality of sleep over the preceding four weeks rated on a six-point Likert scale from 0) not at all to 5) 22–31 days a month. Items regard 1) trouble falling asleep, 2) trouble staying asleep, 3) frequent awakenings during the night, and 4) subjective feelings of fatigue and sleepiness despite having had a typical night’s rest. A cut off score of 2 accounts for sleep disturbances, correlating to at least one troubled night a week [67]. The JSS has good internal consistency (Cronbachs alpha: 0,8 [68]) as well as good construct and content validity and reliability [67–70].

#### Pain assessment

*Pain severity*: Pain severity will be assessed via the pain severity subscale of the Multidimensional Pain Inventory (MPI-D) [44]. This subscale summarizes the items pain now, pain in the last week and suffering related to pain. The MPI-D is a valid instrument with a high reliability (Cronbach’s α ≥ 0.90).*Pain drawings*: Pain drawings will be used to quantify the spatial extent of pain. Drawings will be recorded on an Android device (Android Galaxy Tab S6) using a special stylus pen and the app "Squid" (version: 3.5.0). Participants are asked by the neurophysiological investigator to mark all painful areas of their body on a provided body figure (two schemes—front and back view). To ensure that patients did not focus only on their main pain, the instruction stated, "Mark all areas where you have pain (That is, all affected areas, not just the back!). Mark the overall area where the pain occurs." After completion the pain drawing, the participant and physician discuss it together to eliminate any misunderstandings. The created pain drawings are extracted as image files. The area of the extracted pain areas is calculated by counting the number of pixels and relating them to the area of the filled body template, resulting in percentages of spatial pain extent. Areas will be calculated using the Analyze function in ImageJ.

#### Physical performance

*Six-minute walk test distance.* The participants’ aerobic performance capacity was assessed by submaximal exercise testing (6-min walk test distance; 6-MWTD) in which the walked distance in 6 min along an indoor flat 35-m corridor was calculated and interpreted (poor prognosis if the walked distance is 300 m or less) [45].*Hand grip test*: Muscle fatigue and fatigability will be assessed by ten repeat hand grips at maximum force. The HGT is performed twice, once at the beginning of the assessment (F_1_), and repeatedly after 60 min (F_2_). Based on these values we will calculate the Maximum Force (F_max_), Mean Force (F_mean_), as well as the Fatigue Ratio (F_max_/F_mean_) and the individual Recovery Rate (F_2mean_/F_1mean_). We will measure the hand grip strength (HSG) using a digital hand dynamometer (GRIPX B07RZWB57J). For this, participants must sit in an upright position and place the forearm of the dominant hand in full supination on a standard table. Before starting the measurement, all participants have the opportunity to pull the handle twice to familiarize themselves with the device. The grip is pulled with maximum force for three seconds, followed by a five-second relaxation period under the supervision of the study assistant. Within one session, this procedure is repeated ten times with the dominant hand. The participants are verbally motivated during the measurement to continue using their maximum force and to perform all repetitions. The dynamometer measured the highest value reached within three seconds (force measurement in kg). The mean grip strength of all ten trials will be calculated for baseline values (F_mean_). The test with the highest measured value from the ten repetitions is scored as the maximum force (_Fmax_). For quantifying the degree of fatigability will use the ratio of the maximum force and the mean force (F_max_/F_mean_) with higher values indicating stronger decrease of force within one session. For quantifying the recoverability, we will use the ratio of the mean force from the first testing and the second testing (F_2mean_ / F_1mean_) with lower values indicating impaired recovery [46].In order to obtain data about physical activity from everyday life and promote physical activity [71], the patients were given a pedometer (NAKOSITE LUX2433) to take home. The device counted the steps every day during the study and steps taken were read out and documented by therapists at each training session.

#### Mental performance

To assess neurocognitive function, we will employ several brief tests.*Trail Making Test*: The Trail Making Test (TMT) provides information on visual search, scanning, speed of processing, mental flexibility, and executive functions [72, 73]. The TMT consists of two parts. TMT-A requires an individual to draw lines sequentially connecting 25 encircled numbers distributed on a sheet of paper. Task requirements are similar for TMT-B except the person must alternate between numbers and letters (e.g., 1, A, 2, B, 3, C, etc.). The score on each part represents the amount of time required to complete the task.*Stroop-Test*: The Stroop-Test is a measure used in both—experimental and clinical purposes [74]. It assesses the ability to inhibit cognitive interference, which occurs when the processing of a stimulus feature affects the simultaneous processing of another attribute of the same stimulus. Subjects are required to read three different tables as fast as possible. Two of them represent the “congruous condition” in which participants are required to read names of colors (henceforth referred to as color-words) printed in black ink and name different color patches. Conversely, in the third table, named color-word condition, color-words are printed in an inconsistent color ink (for instance the word “red” is printed in green ink). Thus, in this incongruent condition, participants are required to name the color of the ink instead of reading the word. In other words, the participants are required to perform a less automated task (i.e., naming ink color) while inhibiting the interference arising from a more automated task (i.e., reading the word). Interference is expressed as the difference between the times on these two types of cards. Total time per card divided by number of stimuli on the card occasionally is used to estimate time per stimulus [75].*N-Back Task*: The N-Back task is a continuous performance task that is used to measure working memory [76]. In the N-Back task, participants are presented a sequence of stimuli one-by-one. For each stimulus, they need to decide if the current stimulus is the same as the one presented *N* trials ago. The *N* can be 1 trial, 2 trials, 3 trials, etc. [77].*Digit Span*: The Digit Span test is a subtest of the Wechsler Adult Intelligence Scale (WAIS) as well as of the Wechsler Memory Scales (WMS) [78, 79]. Subjects are asked to read a sequence of numbers and asked to repeat the same sequence back to the examiner in order (forward span) or in reverse order (backward span). Forward span evaluates the efficiency and capacity attention. Backward span is an executive task particularly dependent on working memory. The Digit Span subtest can be scored as one summary value (age-normed and contributing to summary scores in the Wechsler tests), or separately for forwards and backwards performance [78].

#### Treatment expectation and satisfaction, compliance, and acceptability

*Treatment Expectation Questionnaire (TEX-Q):* The Treatment Expectations Questionnaire (TEX-Q) is a generic, multidimensional self-report scale for assessing patient expectations of medical and psychological treatments and allows comparison of the effects of multidimensional expectations across medical conditions [80].*Igroup Presence Questionnaire (IPQ)*: The Igroup Presence Questionnaire (IPQ) is a scale that measures the feeling of presence in a virtual environment (VE). The current version of the IPQ consists of three subscales and an additional general item that is not assigned to any subscale. The three subscales concern the following dimensions 1) Spatial Presence—the feeling of being physically present in the VE, 2) Involvement—measuring the attention paid to the VE and the involvement experienced and 3) Experienced Realism—measuring the subjective experience of realism in the VE. The additional general item assesses the overall "feeling of being there." [36, 37].*Severe adverse events (SAEs):* SAEs will be documented and reported descriptively.*Dropouts*: Dropouts will be analysed according to the underlying reason for dropout and distinction will be made between dropouts preventable and not preventable by modification of study design.

### Retention

We will continuously monitor the trial for any operational issues (i.e., failure in appointment management, no-show of patients). To encourage manageme at each study timepoint, non-responders will receive up to five reminders in total via phone, mail, and e-mail. These reminders will offer the option of being mailed a hard copy of the questionnaire to complete and return via reply paid envelope and/or filling in the FSS alone.

### Statistical methods

Descriptive statistics (absolute and relative frequencies for categorical variables and measures of position (mean, median) and variability (standard deviation, interquartile range, and range) for continuous variables) will be used to compare participant characteristics between the study arms at baseline. Additionally, baseline characteristics will be analysed in patients who discontinue the study.

The analysis of the primary outcome is conducted in the full analysis set following the intention-to-treat principle so that all randomised patients are analysed. Missing values will be imputed by multiple imputation with the fully-conditional specification method [81]. In a sensitivity analysis, the per-protocol population is analyzed, which includes only patients in whose cases the integrity of the intervention (criteria 1–4) is met. Additionally, a complete case analysis will be performed meaning that the analysis of the primary endpoint is repeated in the subset with no missing values for the primary endpoint or relevant covariates. In another sensitivity analysis, we will exclude unmasked patients from the analysis, to assess the impact of unmasking patients. Furthermore, to evaluate the potential influence of at-home aerobic training, we will conduct an additional sensitivity analysis. This will involve adjusting for at-home aerobic training as a co-variable to discern its impact on outcome variables. Lastly, we will execute another sensitivity analysis where patients who were unmasked are excluded, assessing the effect of unmasking on the results.

The null hypothesis for the primary outcome is: The mean absolute change in fatigue symptom severity from T0 to T1 is the same in both groups. The null hypothesis will be tested using a linear regression model at a significance level of 5%. In addition to the group variable, the regression model will contain the following variables at baseline: fatigue symptom severity and age (fixed effects). We will compute effect sizes and interpret them together with the respective 95% confidence intervals [82]. The analyses of the secondary outcomes will be purely exploratory and analogous to the analysis of the primary outcome. We will conduct subgroup analyses for the primary and secondary outcomes applying linear regression models, which will also contain an interaction term between the study arm (intervention vs. comparison) and the subgroup to be investigated. The corresponding *p*-values of these tests will be interpreted purely descriptively. The entire statistical evaluation will be performed in R (version 4.0.2 or higher) [83]. Prior to all analyses, we will pre-specify a statistical analysis plan.

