#### Secondary outcomes

Secondary outcomes include the difference in groups in absolute change in FSS score from T_0_ to follow-up at three (T_2_)- and six-months (T_3_) after end of intervention. At T_1_, as well as at T_2_ and T_3_, we will also calculate the absolute change from T_0_ in depressive and anxiety symptom severity (HADS) [40], Post-exertional Malaise (PEM) [41], Post-COVID-scale of functional status [25, 27], Sleep problems with the Jenkins sleep scale (JSS) [42], physical activity with the exercise vital sign [43], pain severity on the MPI-D [44], the Six-minute walk test distance [45] and the hand grip test [46], performance in the concentration and memory tasks, respectively along with burden of specific somatic complaints (Somatic Symptom Disorder–B Criteria Scale, SSD-12) [47, 48] and the Somatic-Symptom-Scale-8 (SSS8) [49], health-related quality of life (SF-12 questionnaire) [50], and EQ-5D 5L [51] and overall impression of change on the patients global impression of change and therapists global impression of change (PGIC, TGIC).

An additional secondary endpoint is the fatigue level responder status at T_1_. Patients with a reduction in fatigue severity of ≥ 15% are classified as responders. This cutoff is consistent with current recommendations for minimal important differences for fatigue patient reported outcome measures [52–54].

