### Sample size calculation

Given that this is an explorative trial no formal sample size calculation was performed. However, based on recent data from an intervention study [55] in patients with Post-COVID-associated complaints, in which an FSS post-treatment of 5.0 (SD = 1.4) vs. 3.4 (SD = 1.7) between groups was observed, a mean difference of 0.9 (SD = 1.5) is assumed as a conservative effect considering that no active therapy was offered to the control group in this study. With a sample size of n = 45 per group 80% power is achieved to reject the null hypothesis of equal means assuming a mean difference of 0.9 (SD = 1.5) with a significance level of 5% using a two-sided two-sample t-test. Assuming a drop-out rate of 10%, n = 50 per group will be included. The sample size calculation is based on testing the primary hypothesis that immersive VR-based training therapy leads to a significantly different change in mean fatigue severity score (FSS) from baseline to follow-up assessment (T1) as compared to conventional training therapy in the comparison arm. A difference of 0.45–0.88 points on the FSS is considered clinically relevant [56]; we conservatively define the margin of 0.9 as the minimal clinically relevant difference for our trial. Based on previous post-COVID research [55] we assume a common standard deviation of 1.5 among FSS- fatigue scores.

With a sample size of 45 in the experimental group (immersive neuromuscular training) and 45 in the control group (non-immersive physical activity training), a two-sided test for the difference between two means with a 0.05 significance level has 80% power to detect a difference of 0.9 when the standard deviation is 1.5. Assuming a dropout rate of 10%, we will randomize 100 participants, 50 to each condition.

Sample size calculation was performed in PASS 16.0.12.

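### The model for the non-FSS secondary change outcomes is fixed only by analogy to a model adjusted for FSS and age, so it is unclear whether each outcome's own baseline value enters

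*Protocol article*

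**What the plan says.** All references are to the protocol article; the statistical analysis plan that it promises is not shown.

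- **Primary model (Statistical methods).** The null hypothesis is: "The mean absolute change in fatigue symptom severity from T0 to T1 is the same in both groups". It is tested by linear regression and, besides the group variable, "the regression model will contain the following variables at baseline: fatigue symptom severity and age (fixed effects".
- **Secondary model (same section).** "The analyses of the secondary outcomes will be purely exploratory and analogous to the analysis of the primary outcome". No covariates are listed for the secondary outcomes.
- **Form of the secondary outcomes (Secondary outcomes).** Besides change in FSS to T2 and T3, the plan states that "we will also calculate the absolute change from T_0_ in depressive and anxiety symptom severity (HADS"; the same sentence goes on to sleep, pain, the 6-minute walk, grip, concentration and memory tasks, SSD-12, SSS8, SF-12 and EQ-5D, among others.
- **Baselines (Data collection).** Participant data are collected in both arms shortly before randomisation.
- **Stratification (Trial design; Allocation).** The strata are FSS severity and age, the same two variables that the primary model names.

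**The concern.** In the primary model, baseline FSS does two jobs: it is the baseline of the outcome being analysed, and it is a stratification factor. For any other outcome the two jobs fall to different variables, and the text does not say which of them the analogy preserves.

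- **Literal reading:** keep the two named covariates and change only the dependent variable. Change in walk distance is then regressed on arm, baseline FSS and age, without baseline walk distance.
- **Swap reading:** replace FSS by the outcome's own baseline. The model is then arm, own T0 value and age, and FSS severity, a stratification factor, drops out.

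Neither reading gives the model with arm, own T0 value, FSS and age. At stake are precision and robustness to chance imbalance for much of secondary objectives 1 and 2: complaints, quality of life, walk and grip performance, concentration and memory. Effect sizes are to be interpreted with their 95% confidence intervals, so interval width matters even where p-values are only descriptive. Fixing the covariates in advance also removes a choice that would otherwise be open across more than a dozen outcomes.

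**Working it through.** **1. The plan's own figure.** Inputs from Sample size calculation: difference 0.9, SD 1.5 (so 0.9 / 1.5 = 0.6 SD), two-sided 5%, 80% power. An exact two-sample t-test needs 44.6, rounded up to 45 per group, with power 80.4% at 45. With 10% dropout, 45 / 0.9 = 50 per group. The figure reproduces. It concerns FSS only and is not affected by this point.

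**2. Inputs for the secondary outcomes.** n = 45 per arm comes from the plan. The correlation ρ between an outcome's T0 and T1 values is not given; 0.3 to 0.9 is assumed. The correlation of baseline FSS with the outcome is not given; it is first taken as 0, then up to 0.5. Outcomes are scaled to SD 1 at both times, assuming equal SDs.

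**3. Residual variance.**

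- Change score without own baseline: 2(1 − ρ).
- Own baseline in the model: 1 − ρ².
- Ratio: (1 − ρ²) / [2(1 − ρ)] = (1 + ρ) / 2.
- Excess interval width without own baseline: √[2 / (1 + ρ)] − 1.

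**4. Chance imbalance.** One standard error of the baseline mean difference is √(2/45) = 0.21 SD. A baseline difference of that size moves the change-score estimate by (1 − ρ) × 0.21 SD, in the opposite direction.

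| ρ (assumed) | 2(1 − ρ) | 1 − ρ² | Ratio | Interval wider by | Shift from 0.21 SD imbalance |
|---|---|---|---|---|---|
| 0.3 | 1.40 | 0.91 | 0.65 | 24% | 0.15 SD |
| 0.5 | 1.00 | 0.75 | 0.75 | 15% | 0.11 SD |
| 0.6 | 0.80 | 0.64 | 0.80 | 12% | 0.08 SD |
| 0.7 | 0.60 | 0.51 | 0.85 | 8% | 0.06 SD |
| 0.8 | 0.40 | 0.36 | 0.90 | 5% | 0.04 SD |
| 0.9 | 0.20 | 0.19 | 0.95 | 3% | 0.02 SD |

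At ρ = 0.6 the difference detectable with 80% power, 2.80 × √(2 × variance / 45), falls from 0.53 to 0.47 SD when the own baseline is added.

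**5. Does adjusting for FSS already do the work?** No. With FSS correlations up to 0.5, the excess width runs from about 2% (ρ = 0.9) to 37% (ρ = 0.3).

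**6. Simulation check.** 4,000 runs, 45 per arm, ρ = 0.6, FSS correlated 0.3 with both T0 and T1 values, no treatment effect. Standard error 0.193 SD without and 0.171 SD with the own baseline (variance ratio 0.79). The correlation of the estimate with the baseline imbalance is −0.45 without and about 0 with it. Both mean estimates are about 0, so neither is biased.

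**7. Swap reading.** With the correlations of step 6, the residual variance is 1 − 0.6² = 0.64 with own baseline only and 0.624 with FSS added; √(0.64 / 0.624) − 1 is about 1%. Dropping FSS costs little precision in this example, but the model then no longer reflects the stratification.

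**The case against.** The strongest reply is that *analogous* most naturally means the outcome's own baseline. FSS is the primary outcome's own baseline, so the counterpart for walk distance is baseline walk distance. This stands as far as it goes: a reader might infer that the plan will omit the own baseline, and the document does not establish that. But the named covariates are also the stratification factors, so keeping them unchanged is an equally workable reading, and the swap loses one of them.

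Second, covariate lists for exploratory outcomes are ordinary content of an analysis plan, and one is promised. That is fair, and it keeps the point small. Yet the article is not silent: it ties the secondary models to a model with named covariates, and an author of the analysis plan would start from that wording.

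Third, a reader might infer bias, since patients with poor T0 values tend to improve more. That tendency is common to both arms; randomisation keeps both estimators unbiased, as the simulation shows. Only precision and sensitivity to chance imbalance are at issue.

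Fourth, a reader might carry over the 0.6 SD effect from the FSS sample size and claim a gain in power. The documents do not support this: no secondary outcome has a target effect, and 0.6 SD of the change score is a different raw effect at each ρ. Interval width is the safer measure, and at high ρ the loss is slight.

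**Conclusion.** The concern holds as a minor ambiguity with a free improvement. The text leaves open whether the non-FSS change outcomes are adjusted for their own T0 value, and neither of the two main readings yields the model that uses both that value and the stratification factors.

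Under the literal reading, intervals are about 24% to 3% wider than needed for ρ from 0.3 to 0.9 with no FSS correlation. A one-standard-error baseline imbalance shifts the estimate by about 0.15 to 0.02 SD over the same range. These sizes rest on assumed correlations and equal SDs at T0 and T1, because the protocol supplies neither; whether the loss is material for a given outcome cannot be settled from it.

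The primary analysis and the sample size are sound on this point. Change in FSS at T2 and T3 is unaffected, since FSS is its own baseline. PGIC and TGIC have no T0 value. The affected analyses are declared exploratory, so no confirmatory claim depends on them.

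**What to change.** Keep the existing sentence, so that the full analysis set, the multiple imputation and the effect sizes with 95% confidence intervals still carry over to the secondary outcomes. Add after it, in the protocol or the analysis plan:

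> For each continuous secondary change outcome measured at T0, the linear regression model additionally contains the T0 value of that same outcome, alongside study arm, baseline FSS and age.

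The restriction to continuous change outcomes leaves out PGIC and TGIC, the responder endpoint and the ordinal PCFS, for which this sentence should not prescribe a model. For change in FSS at T2 and T3 the added term is baseline FSS itself, so nothing changes there.

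The cost is one sentence and one degree of freedom per model. No new data are needed and the primary analysis is untouched.
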